#### Patient Feedback

Equal proportions of participants in subprotocols 1-3 are being asked to complete a questionnaire related to VS measurement and their preferences. The data are fully anonymized and recorded without any identifiable information (including participant ID code).

#### Clinical Feedback

A questionnaire is available to garner feedback on the technology from the clinical user’s point of view (ie, the nurses who take the VS measurements). Questionnaire and interview data are fully anonymized and recorded without any identifiable information.

#### Health Economics Data Collection

The study also includes activities to obtain information and data to assess the cost-saving potential of Lifelight in different clinical settings, including as a tool to detect undiagnosed cardiovascular disease and to monitor symptoms. The cost of BP monitoring equipment and its maintenance and calibration will also be determined.

Stopwatch observational studies are run to determine how long it takes to measure VS using standard-of-care equipment and Lifelight, starting from the time when the clinician decides to conduct a VS check and incorporating the time it takes to find the measuring equipment, roll up the patient’s sleeve, put on the devices, wait for the result, and put the equipment away. This part of the study will involve approximately 20 participants.

### Privacy and Data Collection

Each study participant is assigned a unique sequential ID; no identifiable data are stored. All documents are stored securely and are only accessible by the study staff and authorized personnel. The code linking the ID to the participant’s personal information is kept within the hospital study site and can only be accessed by the research team.

Full-resolution video data are uploaded during the study. The consent form allows the participants to decide whether data can be shared as full-face video or with identifying features obscured.

Videos collected in the study constitute personal data, as it may be possible to identify participants, but are collected for research purposes only (not clinical care) and are processed within the legitimate interests of Xim Ltd. These data will be protected according to the General Data Protection Regulation.

### Data Handling

For each reading, a high-quality video of the whole face is saved to the internal storage of the iPad in encrypted form. Anonymized rPPG data (the average color of areas of the face) are saved directly and immediately sent to an NHS-compliant cloud server.

Subsequent analysis will be performed using the encrypted files, which are downloaded to a processing site, decrypted, and processed automatically (ie, without any person viewing the videos). This procedure will result in anonymized aggregate data sets. Decrypted files will subsequently be deleted from the processing site.

All protocol-required information besides video data is collected in an electronic case report form. The REDCap electronic cloud is used to store and manage all consent and study data. All data collected about study participants are kept strictly confidential.

### Performance Targets

The accuracy of Lifelight using the training data generated in VISION-D was sufficient to support the certification of Lifelight as a class I CE medical device [15]. However, the accuracy needs to be improved further for use in routine clinical practice. Table 2 lists the performance targets for Lifelight; training data collected during VISION-MD will support the progress toward these targets.

**Table 2 table2:** Performance (accuracy) targets for Lifelight.

Vital signs	Accuracy target	Basis for target
Blood pressure	SBP^a^ can be measured with standard deviation ≤8 mm Hg British Hypertension Society Grade C for SBP measurement	ISO81060-2^b^ for blood pressure cuffs [19]
Pulse rate	Root mean square error of ≤3 beats per minute	Most common accuracy of CE^c^-marked commercially available devices
Respiratory rate	Maximum error tolerance of 5 breaths per minute	Accuracy of Philips Health watch, a CE-marked contact-based photoplethysmography device
Oxygen saturation	Maximum error tolerance of 4%	ISO80601-2-61 standard for pulse oximeters [20]

^a^SBP: systolic blood pressure.

^b^ISO: International Organization for Standardization.

^c^CE: Conformité Européenne.

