Given that only a small proportion of the raw video signal is relevant for rPPG measurement of VS (1%-2%), we are developing ways to enhance data collection and signal processing. Video recordings will be of higher resolution than those in the VISION-V and VISION-D studies, and data processing is focusing on the midface region (cheeks, nose, and top of the lip), rather than the whole face; these areas are computationally efficient for rPPG because of their large area and good-quality signal [16] but are not likely to be affected by autoregulation of cerebral blood flow (which discounts the forehead) [17]. We are also developing a method to identify small regions of interest in the midface in each participant where signal quality is the highest. This approach is expected to overcome some of the challenges of rPPG for routine clinical use, such as positioning of the participant relative to the light source.

VISION-MD (Clinicaltrials.gov NCT04763746) aims to advance the development and accuracy of the Lifelight app as a noninvasive and easy-to-use device to measure VS in hospitals and the community. The study will collect data from a broad range of patients to further develop the accuracy of Lifelight to a level sufficient for clinical applications, including screening and monitoring of cardiovascular disease. The initial data collected are being used for machine learning; later data will be used to test the accuracy of Lifelight compared with standard-of-care measurement of VS.

Thus, the primary objective of VISION-MD is to further develop the Lifelight algorithms across extensive clinical ranges, including critically ill patients and in patients with different skin tones. Secondary objectives are: (1) to improve and test the efficacy of Lifelight estimates for BP, pulse rate, respiratory rate, and oxygen saturation in multiple clinical settings (eg, critical care, outpatient clinics, and general hospital wards); (2) to evaluate the impact of variables on the accuracy of Lifelight VS measurements (eg, age, sex, temperature, health condition, medication, skin tone, and ambient lighting); (3) to understand the health economic potential of Lifelight; and (4) to compare the patients’ experience of current contact-based methods for measuring VS and Lifelight and to evaluate the patients’ acceptance and appetite for Lifelight.

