3	35	Approximately 33% with SOC-measured oxygen saturation <88%, 88%-92%, and 93%-95%	Ideally, each band will include participants with each skin tone
4	No specific target; likely to be a small proportion	N/A	N/A

^a^Participants in subprotocol 4 (ie, those without the capacity to provide informed consent) are likely to have vital sign values outside of the normal range and will contribute to all subprotocol targets. Only the first study session per participant contributes to the sample size.

^b^SOC: standard of care.

^c^SBP: systolic blood pressure.

^d^Can include participants with SBP measured from an arterial line.

^e^N/A: not applicable.

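### Table 2 leaves three accuracy targets poorly specified: the SBP figure ignores systematic error, the RR and SpO2 tolerances name no statistic, and a pooled SpO2 result would say little about low values

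*Protocol article*

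**What the plan says.** The Data Analysis section states that the test data will be used to judge Lifelight against Table 2 (Performance Targets). The table's rows use different kinds of criterion:

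- **Blood pressure:** SBP "can be measured with standard deviation ≤8 mm Hg", followed in the same cell by "British Hypertension Society Grade C for SBP measurement". The basis given is ISO81060-2. Nothing joins the two parts, and there is no diastolic entry.
- **Pulse rate:** "Root mean square error of ≤3 beats per minute".
- **Respiratory rate:** "Maximum error tolerance of 5 breaths per minute".
- **Oxygen saturation:** "Maximum error tolerance of 4" (percent).

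The secondary objectives in the Introduction are wider than the blood pressure row. The first is "to improve and test the efficacy of Lifelight estimates for BP, pulse rate, respiratory rate, and oxygen saturation", without restriction to systolic pressure.

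Under Sample Size, about 250 of 1950 participants are for testing, and the training/test split is to be settled during the study. Table 3 targets 1500, 375 and 35 participants in subprotocols 1, 2 and 3. Low SpO2 is targeted only in subprotocol 3: "Approximately 33% with SOC-measured oxygen saturation <88%, 88%-92%, and 93%-95" percent.

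**The concern.** Table 2 is the study's decision rule, so its wording determines what may be declared on target. There are three weaknesses.

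1. **SBP.** An SD describes scatter about the mean error and is unchanged by adding a constant to every reading. Alone, it lets a biased device through. The neighbouring pulse-rate row would not, so the table is not consistent with itself. If the grade is an alternative to the SD, bias is unlimited on the SD route. If both are required, the grade may limit bias, but the article does not say which applies.
2. **RR and SpO2.** A maximum error tolerance could mean that every reading must lie inside it, that some share must, or that a summary error must. These are different tests, and the choice could be made after the results are seen.
3. **Low SpO2.** On any pooled reading of the SpO2 tolerance, normal values dominate. The study exists partly to obtain values outside the normal range, and those are the values a pooled SpO2 result would hardly test.

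**Working it through.** **The plan's own figures.** 1700 + 250 = 1950, as stated. The Table 3 targets sum to 1500 + 375 + 35 = 1910, within 3% of 1950. Subprotocol 4 has no target.

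**1. SBP: what the SD limit lets through.** Inputs: SD 8 mm Hg (Table 2), normal errors (assumption), and a range of constant offsets b (assumption). RMSE = √(b² + 8²). Share within 5 mm Hg = Φ((5 − b)/8) − Φ((−5 − b)/8).

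| Offset b (mm Hg) | RMSE | Within 5 mm Hg |
|---|---|---|
| 0 | 8.0 | 47% |
| 5 | 9.4 | 39% |
| 10 | 12.8 | 24% |
| 15 | 17.0 | 10% |
| 20 | 21.5 | 3% |

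All five rows meet SD ≤8. At b = 10, for example, √(100 + 64) = 12.8.

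**2. RR: dependence on the number of readings under a literal maximum.** RR is measured in subprotocols 2 and 4 only (Table 1). In a proportional test set, subprotocol 2 supplies 250 × 375/1910 = 49 participants. Table 1 gives two measurements each, so 98 readings. The article gives no error SD, so a range is shown, with unbiased, normal, independent errors assumed. P(all within 5) = [2Φ(5/SD) − 1]ⁿ.

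| Assumed error SD | One reading within 5 | 49 readings | 98 readings |
|---|---|---|---|
| 1.5 | 99.9% | 96% | 92% |
| 2 | 98.8% | 54% | 29% |
| 3 | 90.4% | 0.7% | <0.1% |

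At SD 2, 0.9876⁴⁹ = 0.54 and 0.9876⁹⁸ = 0.29. If two readings on one person have positively correlated errors, the value for 98 lies between 29% and 54%. Either way, the same device is less likely to pass the more it is tested.

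**3. SpO2: what a pooled reading shows.** A constant 97% is within 4 points of every reference value from 93% up. In subprotocol 3, two of the three bands lie below that: 35 × 2/3 ≈ 23 participants. A proportional test set holds 250 × 35/1910 = 4.6 participants from subprotocol 3, of whom 250 × 23/1910 = 3.0 are at 92% or below. How many others are low is not given, so the share q of the 1875 participants in subprotocols 1 and 2 at 92% or below is varied (assumption). The share within tolerance is 1 − (23 + 1875q)/1910.

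| q | Participants outside tolerance | Constant 97% within 4 points |
|---|---|---|
| 0 | 23 | 98.8% |
| 1% | 42 | 97.8% |
| 3% | 79 | 95.9% |
| 5% | 117 | 93.9% |

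Within subprotocol 3 alone, the same constant is in tolerance for only 12 of 35, or 34%. The high pooled agreement therefore comes from the mix of participants.

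**The case against.** A reader might infer that a device that does not work could pass Table 2. The documents do not support that. Subprotocol 1 plans about 100 participants in each of 13 SBP bands from below 90 to above 200 mm Hg. A constant output over those bands has an error SD of about 37.5 mm Hg, or 34.9 if the 200 participants beyond 13 × 100 all sit at the centre, against a limit of 8. It also fails the pulse-rate RMSE unless the reference pulse SD is 3 or less. Passing SD ≤8 requires real tracking, so the SBP gap concerns a device that tracks with an offset.

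Other stronger readings also go too far:

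- **A constant RR passes.** This needs an RR spread the article does not give. A constant at the mean is within 5 for 98.8%, 90.4% and 78.9% of readings at an RR SD of 2, 3 and 4.
- **A constant SpO2 meets the tolerance as written.** Under a literal maximum it probably fails, since one participant at 92% or below defeats it. The chance that a proportional draw of 250 has none of the 23 is about 0.04.
- **Diastolic pressure will not be tested.** The objective covers blood pressure generally. What is missing is a diastolic target.

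The strongest remaining defence is that the grade and the cited ISO standard may both limit mean error, and that a table extracted from a PDF may have lost a line break between the two SBP criteria. Their thresholds are not in the article, so this can be neither confirmed nor excluded, and the lack of a bias limit is shown only for the SD figure. It is also fair that subprotocols 1, 2 and 4 could add low SpO2 values, so about 3 of 250 is nearer a floor, and that band-wise reporting may sit in the full protocol or analysis plan. Those documents could supply the detail, but the targets published here are the declared criteria and remain ambiguous as worded.

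**Conclusion.** The point holds as a defect in how three stated targets are worded, and it should be corrected. The SBP number permits an offset: at 10 mm Hg with SD 8, RMSE is 12.8 and half as many readings fall within 5 mm Hg as without bias (24% against 47%). Whether the grade closes this gap cannot be told from the article. Diastolic pressure has no target although the objective names blood pressure.

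The RR and SpO2 tolerances do not define a pass. Under a literal maximum, a device with RR error SD 2 passes 54% of the time on 49 readings and about 29% on 98. Those figures rest on the assumed SD and independent errors, but the dependence on the number of readings does not rest on the particular SD.

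The literal and pooled readings of the SpO2 tolerance are alternatives with opposite faults, and the wording does not choose between them. If pooled, the result says little about low saturation: a constant 97% is in tolerance for about 94% to 99% of participants, assuming 0% to 5% of subprotocols 1 and 2 are at 92% or below and leaving subprotocol 4 aside. About 3 of 250 test participants would come from the two lower bands under a proportional draw, and the article reserves none for testing.

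**What to change.** - **SBP:** beside SD ≤8, require a mean-error limit taken from the standard the table cites, or an RMSE limit. State that the SD and Grade C criteria are both required.
- **Diastolic pressure:** add a target, or limit the blood pressure claim to SBP.
- **RR and SpO2:** replace the maximum error tolerance with RMSE plus mean error, judged by reference band as well as overall. The band-wise part is essential, because a pooled RMSE is also dominated by normal values.
- **Held-out set:** before the split is made, reserve a fixed share of low-SpO2 participants for testing, or limit the SpO2 claim to the range actually tested.

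The cost is new wording in Table 2 and Data Analysis and a rule for drawing the test set, with no extra recruitment. The targets become harder to meet, and a few of the scarce low-SpO2 participants leave the training data. With so few of them, band-wise SpO2 results will be imprecise and should be reported as such.

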#### VS measurement

The study staff ensure that participants have been at rest for at least 10 minutes before VS measurement starts and that they have not consumed any food or drink in the previous 30 minutes (other than intravenous fluids or nasogastric feeding). In each study session, VS is measured as per the subprotocol using the standard-of-care equipment while simultaneously capturing a video of the participant’s face using the Data Collect app running on a tablet (standard iPad 9.7, 2018) positioned approximately 1 m away and angled toward the participant’s face. Controls and instructions on the device start and stop the 60-second video recording. Background luminosity is measured using a handheld lux meter. The study staff have been briefed on the optimum Lifelight measurement conditions. Recordings are repeated once or twice, as set out in Table 1. The app does not return any measurements to the user or participant.

VS measurements are taken and coordinated by 2 nurses, one of whom announces the start and finish of the recording period on the Data Collect app. BP is measured using a standard clinical automatic sphygmomanometer with an appropriately sized cuff (width at least two-thirds of upper arm length) on the participant’s nondominant upper arm (unless contraindicated) or via an arterial line if fitted. BP is recorded at the start of the recording period. A standard clinical finger clip sensor for the measurement of oxygen saturation and pulse rate is placed on a finger on the opposite side of the body to the sphygmomanometer. Oxygen saturation and pulse rate are measured at 0, 30, and 60 seconds of the recording period and averaged. Respiratory rate is determined manually by counting chest rises throughout the 60-second period. The nurse may place their hand on the participant’s chest to increase the accuracy of manual counting but being mindful not to obscure the camera’s line of sight.

Each study session takes approximately 30 minutes. Once the measurements are completed, the study staff complete the postmeasurement observation questions relating to how much the participant moved, their position, whether they were wearing glasses, any hairstyle or other item (eg, face covering) that obscured any part of their face during the recording, and whether the software reported “face not found” at any point during the recording.

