### Sample Size

The sample size cannot be formally calculated because it depends on the incremental improvement in the accuracy of Lifelight achieved through machine learning using the training data generated in the study. However, indicative sample sizes for the 4 subprotocols have been calculated by assessing the optimal data requirements to enable algorithm training toward the standards defined in Table 3, balanced against the practicality of achieving the targets. The split between training and testing data will be determined during the study according to the quality of the data collected.

The initial protocol anticipated data collection from about 8400 participants for training and a further 1000 for independent testing of accuracy, but the recruitment has been compromised by restrictions implemented during the COVID-19 pandemic. However, the high-quality video recording (compared with VISION-D and VISION-V) supported a protocol amendment to reduce the recruitment to 1950 participants (see Results section), with the expectation that data from about 1700 will be used for training the algorithms and data from 250 used for testing. The study management team is monitoring the progress of data collection and accuracy, and updates the study teams monthly. The study will continue until the accuracy of Lifelight for measuring VS is sufficient for various clinical use cases.

As skin tone is expected to affect the accuracy of Lifelight, the aim is to recruit participants across the full Fitzpatrick skin tone scale (1-6). To allow the impact of skin tone measurement accuracy to be determined with statistical robustness, the full data set will be sampled to create a subset for skin tone analyses in which the prevalence of the usually less prevalent skin tones is amplified. This subset will contain 750-1000 measurements, with 15%-20% each from categories 1, 2 and 3, 4, and 5 and 6. These measurements should be spread across the subprotocols as indicated in Table 3.

**Table 3 table3:** Indicative sample size targets.

Subprotocol	Indicative sample size, n^a^	Characteristics	Participants with skin tone categories 1, 4, 5, and 6
1	1500	Roughly 100 participants will be recruited with SOC^b^-determined SBP^c^ in each 10 mm Hg increment from <90 mm Hg to >200 mm Hg (ie, <90 mm Hg; 90-99 mm Hg; 100-109 mm Hg, etc)^d^	Ideally ≥4 in each SBP band
2	375	N/A^e^	Ideally ≥10 in each SBP band

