### Data Analysis

The training data will be used to further develop the signal extraction and processing methodology. The test data will subsequently be used to determine the performance of Lifelight against the targets set out in Table 2.

All statistical analyses will be performed using Microsoft Excel. All analyses will be completed per protocol since there is no intention to treat.

There will be no imputation of missing or implausible data, and any missing, implausible, or problematic readings will be excluded from the analysis. If the Lifelight software is unable to detect the participant’s face during the measurement period, this will be recorded in the electronic case report form, and the measurements will be deleted from the data set.

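### The respiratory-rate and SpO2 targets name no summary statistic; read literally, one worst reading decides each verdict and the chance of passing falls as the test set grows

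*Protocol article*

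**What the plan says.** Table 2 (Performance Targets) has four rows. Two name a summary statistic: systolic pressure "can be measured with standard deviation ≤8 mm Hg", and pulse rate by "Root mean square error of ≤3 beats per minute". The other two give only a limit: "Maximum error tolerance of 5 breaths per minute" for respiratory rate and "Maximum error tolerance of 4" percent for oxygen saturation. The basis column cites the accuracy of a contact device for the first and a pulse-oximeter standard for the second. The article does not say what share of readings must lie within either limit, or whether the limit applies to a reading, a participant or a summary.

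The table is the yardstick for the evaluation. Under Data Analysis, "The test data will subsequently be used to determine the performance of Lifelight against the targets set out in Table 2".

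The number of test readings is not fixed. Sample Size expects that "data from about 1700 will be used for training the algorithms and data from 250 used for testing", but also says that "The split between training and testing data will be determined during the study according to the quality of the data collected". Each session yields more than one reading: "Recordings are repeated once or twice, as set out in Table 1". Data Analysis also drops readings judged implausible or problematic, without a numerical definition.

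**The concern.** An SD or an RMSE estimates a fixed property of the device, and more readings only make the estimate more precise. The largest error in a sample has no such fixed target: it tends to grow with the number of readings. If the two rows are applied as written, the verdict mixes the device's accuracy with the size of the test set. The same device could meet the target in a small test set and miss it in a larger one, and keeping or dropping one extreme reading could reverse the result.

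At stake is the verdict on respiratory rate and oxygen saturation under secondary objective 1. The primary objective, algorithm development, is not affected.

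**Working it through.** **No stated figure to reproduce.** The article gives no pass probability, error SD, alpha or power for these rows. Its participant total does add up: 1700 + 250 = 1950.

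**Literal rule.** The target is met only if every absolute error among n test readings is at most T. For independent, unbiased normal errors with standard deviation SD:

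P(meet) = [1 − 2(1 − Φ(T/SD))]^n

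**Inputs.**
- T = 5 breaths/min and T = 4 points (Table 2).
- SD is an assumption and is varied.
- n is also an assumption. It takes the 250 test participants to follow the Table 3 targets (1500 + 375 + 35 = 1910) and every first-session recording to be scored.
- Respiratory rate is measured in subprotocol 2, two readings each (Table 1): 250 × 375/1910 ≈ 49 participants, × 2 = 98 readings. Subprotocol 4 also measures it, but has no numerical target and is left out.
- SpO2 is measured in every subprotocol: (1500 × 3 + 375 × 2 + 35 × 2) × 250/1910 = 5320 × 250/1910 ≈ 696 readings.

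**Respiratory rate, limit 5**

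| SD | Readings within limit | n = 49 | n = 98 | n = 250 |
|---|---|---|---|---|
| 1.5 | 99.9% | 96% | 92% | 81% |
| 1.67 | 99.7% | 87% | 76% | 50% |
| 2.0 | 98.8% | 54% | 29% | 4% |

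**SpO2, limit 4**

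| SD | Readings within limit | n = 35 | n = 250 | n = 696 |
|---|---|---|---|---|
| 1.0 | 99.99% | 99.8% | 98% | 96% |
| 1.33 | 99.7% | 91% | 52% | 16% |
| 1.5 | 99.2% | 76% | 15% | 0.5% |

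**Break-even.** The chance of passing is 50% at a respiratory-rate SD of 1.86 (n = 98) or 1.67 (n = 250), and at an SpO2 SD of 1.34 (n = 250) or 1.22 (n = 696).

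**Without normality.** If 1 reading in 100 exceeds the limit, independently, P(meet) = 0.99^n, which is 37% at n = 98 and 8% at n = 250. If 1 in 1000 exceeds it, P(meet) = 0.999^n, which is 91% and 78%.

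**Repeats in one person.** Simulated with a within-person correlation of 0.5 to 0.8, respiratory rate at SD 2.0 (49 people × 2 readings) passes 31% to 36% of the time, against 29% under independence. SpO2 at SD 1.5 (250 people × 3 readings) passes less than 2% of the time. The independence assumption does not drive the result.

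**Named statistics, same limits.** The respiratory-rate device with SD 2.0 that passes the literal rule 29% of the time at n = 98 meets RMSE ≤ 5 almost always. It meets 95% limits of agreement within ±5 more than 99% of the time. A poor device still fails the limits-of-agreement rule: respiratory rate with SD 3 at n = 98 passes less than 1% of the time.

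**The named statistics are not interchangeable.** With zero bias, limits of agreement within ±4 need SD ≤ 4/1.96 = 2.04, while RMSE ≤ 4 allows SD up to 4. At SD 4 with normal errors, 2(1 − Φ(1)) = 32% of readings lie outside 4 points.

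**The case against.** The strongest reply is that the authors may not intend a worst-reading rule. The wording can mean the largest allowed value of an accuracy figure taken from the cited basis, and nothing in the article says that one exceedance fails the device. The full protocol or analysis plan, not shown here, may name the statistic. This stands as far as intent goes: a reader should not infer that the authors mean to fail the device on one reading. But on that reading the two rows set a ceiling on a statistic that the article does not name, next to two rows that do name one. The choice can decide the verdict, as the SD 2.0 example shows, so the correction is the same.

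A reader might also infer that an accurate device is likely to fail. The article does not support this, because it gives no error SD. At SD 1.5 for respiratory rate (n = 98) or SD 1.0 for SpO2 (n = 696), the device passes more than 90% of the time even under the literal rule.

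It is tempting, too, to say that one outlying finger-clip value could alone fail the SpO2 target. Under VS measurement, the SpO2 reference is the average of three values, so one of them would have to be wrong by more than 3 × 4 = 12 points to move the reference by more than 4. That argument is weak and is not relied on here.

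Finally, the calculation uses untrimmed normal tails, whereas the plan drops implausible or problematic readings. Trimming would raise the chance of passing by an amount that cannot be stated, because the exclusion has no numerical definition. It also means the verdict would depend on which readings are dropped.

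**Conclusion.** The point holds as a defect in how two of the four performance targets are specified. As worded, they name no statistic. On the plain reading they are a worst-case rule whose result depends on a test-set size that is settled during the study.

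The size of the problem depends on the unknown error SD. It is small if SD is at or below about 1.5 breaths/min (n = 98) or 1.0 point (n = 696). It is decisive at 2.0 breaths/min or 1.5 points, where about 99% of readings are inside the limit but the chance of meeting the target is 29% or 0.5%. These figures assume unbiased, independent normal errors, Table 3 proportions in the test set and separate scoring of every repeat. Bias or heavier tails would lower the chances; fewer scored readings would raise them. It is not shown that Lifelight itself would fail.

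The change should be made, because it is cheap and loses credibility once the test results have been seen.

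**What to change.** Before the test data are opened, replace the maximum-error wording in both Table 2 rows with a named statistic that does not depend on the number of readings. RMSE, as in the pulse-rate row, or 95% limits of agreement (bias ± 1.96 SD of Lifelight minus reference) within the stated limit would both serve. The choice must be matched to the cited basis, because the two set very different bars at the same limit. State the unit of analysis, including how repeat readings in one participant are handled. Give a confidence interval for the statistic, since the respiratory-rate test set may be only about 49 people. Report the largest error descriptively only.

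The cost is the wording of two table rows and a sentence or two under Data Analysis; no new data are needed. The downside is that some readings may exceed the limit without failing the target: up to about 5% under limits of agreement with normal errors, and more under RMSE. That is why the largest error should still be shown.
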